### 2.7. Data Analysis

Quantitative data will be analyzed in concordance with the CONSORT guidelines [46]. The baseline demographic and clinical characteristics of the two groups will be analyzed using Chi-squared, Fisher’s Exact, and Student’s *t*-tests. The primary (clinical mental health outcomes) and secondary outcome (health services utilization) measures will be analyzed using descriptive and inferential statistical analysis, and Bonferroni correction will be used when necessary. The scores at each time point on standardized rating scales for clinical variables (PHQ-9, GAD-7, WHO Five Well-Being Index, BRS, RAS, ACE, C-SSRS, and BSCS) will each be compared between the intervention and control groups using an analysis of covariance (ANCOVA) with the treatment condition as the independent variable, the baseline scores on clinical variables as the covariate, and the scores at each time point on standardized rating scales as the dependent variable. In each case, checks would be conducted to ensure the reliable measurement of the covariate and no violation of the statistical assumptions of normality, linearity, homogeneity of variance, and homogeneity of regression slopes. Multiple imputations will be our baseline approach to addressing missing data, although analysis of missingness patterns must be performed to inform our specific assumptions, implementation, and interpretation during missing data analysis. Sensitivity analyses will also be conducted with respect to the imputation approach, including a comparison with the last observation carried forward, mean/median imputation, best case, worst case, and complete case analyses. The reasons for discrepancies between approaches will be analyzed and discussed in the study manuscript. We will also compare the prevalence scores for the clinical variables of interest using Chi-square/Fisher’s exact tests. To explore the impact of select demographic and clinical variables on the clinical variables of interest, we will perform a two-way between-groups = analysis of variance. Characteristics of individuals/clusters will be summarized by exposure status to allow the consideration of selection biases and lack of balance [47]. In terms of the number of multiply imputed datasets to be analyzed, we will begin with 100 datasets. A sensitivity analysis will subsequently increase this number to ascertain the stability of model estimates in relation to the number of multiply imputed datasets.

Patient satisfaction quantitative data will be analyzed by using one-way analysis of variance (ANOVA) tests to compare satisfaction between the two study groups. Likert scale satisfaction responses to various aspects of Text4Support and freely accessible Health-Authority-approved low-intensity e-mental health services will be summarized as frequency counts of response categories and percentages. We will compare the differences in satisfaction between the groups by using the Chi-square/Fisher exact test with two-tailed criteria. A Bonferroni-corrected, two-tailed criterion (α = 0.05/*n* (*n* = number of comparisons) will be used to determine statistical differences.

Qualitative data analysis will be aligned with qualitative descriptive methods. The qualitative data analysis will be guided using the six-phase thematic analysis framework [26] and conducted by two distinct members of the research team. They will perform an independent analysis and then compare their findings. Data disagreements will be resolved by discussion and convergence, if possible. The remaining disagreements will be resolved by a third researcher and/or documented for discussion in the study report.

The first step of qualitative analysis is to transcribe verbatim all audio records from the semi-structured individual interviews and focus groups and enter them in NVIVO 12 [48] software for data organization and preparation. This step is crucial to becoming familiar with the data, and reading and re-reading the transcripts. At this stage, we will also perform data validation for quality assurance purposes. A data validator, who is a different person from the transcriber, will compare the verbatim transcriptions with the recorded interviews for verbal and non-verbal errors (commissions and omissions). Errors in transcription will be corrected during validation. The subsequent phases of thematic analysis (coding, searching for themes, themes review, themes definitions, and writing) will be accomplished [27]. The sample size for the qualitative sub-study will depend on data saturation [32,33].

The analysis of the implementation outcomes will be guided by the RE-AIM framework (reach of the interventions, acceptability, appropriateness, fidelity, and cost-effectiveness) [28]. We want to look into the context, method, and consequences of deploying Text4Support and compare them. The adoption of the Text4Support intervention will be evaluated using a combination of quantitative and qualitative data, as well as subsequent analysis (as mentioned in the preceding sections).

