### 2.3. Sample Size Considerations

With a hypothesized difference of 20% in change scores (from baseline to the four-time points) for each of the primary outcome variables of interest (e.g., mean change score of 10 vs. 8), a population variance of 5.0 for the mean change score, a 2-sided significance level (α = 0.05), a power of 90% and an acceptable difference between the sample mean and population mean score for each scale of zero (μ − μ0 = 0), an estimated sample size of 131 participants in each arm of the study would be needed (based on the 6Sigma online script) to detect the projected mean differences in mean change scores between the intervention and control groups [29,30]. Thus, the sample size for the RCT would be 262. Given that the maximum survey completion rate for the online surveys delivered via text message is approximately 20%, in order to achieve 262 completed survey responses at each time point, we plan to enrol at least 1500 participants in the RCT. This recruitment rate is achievable since a related study in Alberta [31] currently has over 500 patients recruited within six months. The sample size for the qualitative component of the study cannot be predetermined. Data saturation is reached across data analysis, ending when no new themes and subthemes emerge. However, based on what the literature suggests [32,33], we anticipate that 25–30 participants may be sufficient for this particular mixed-method study.

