#### 2.4.4. Follow-Up Assessment

Participants in both study arms (intervention and control) will receive a link to the follow-up self-completed online surveys through SMS and be asked to complete them at 6 weeks and 3, 6, and 12 months after enrolment in the study. The same clinician-rated scales completed at enrolment will be completed over the phone by a trained research team member. A monitoring compliance strategy will be put into practice (a reminder text message after two days and then phone calls from the research team) in order to mitigate the loss of follow-up and improve patient compliance.

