### 2.6. Outcome Measures

The intervention effectiveness will be determined by evaluating the differences between the intervention and control group from baseline and the subsequent time points (6 weeks and 3, 6, and 12 months) for patient clinical outcomes and the differences between groups for health service utilization at 12 months, and the implementation success will be measured through quantitative and qualitative patient satisfaction data and implementation indicators, as follows:Clinical outcomes: The primary clinical outcome will be the differences in mean change in patient recovery and quality of life, assessed through the Recovery Assessment Scale (RAS) [37] and the World Health Organization Five Well-Being Index (WHO-5) [38]. Secondary clinical outcomes will include the differences between the intervention and control groups in prevalence changes for moderate-to-high depression (likely major depressive disorder), moderate-to-high anxiety (likely generalized anxiety disorder), and low resilience from the baseline to these time points, assessed through the Patient Health Questionnaire-9 (PHQ-9) [39], Generalized Anxiety Disorder-7 scale [40], and the Brief Resilience Scale (BRS) [41]. The mean score differences between groups from the baseline to determine time points will also be assessed using the Adverse Childhood questionnaire (ACE questionnaire) [42], and the Brief Substance Use Craving Scale (BSCS) [43], which will be used to assess childhood trauma and substance craving, as well as the clinician-rated Columbia-Suicide Severity Rating Scale (C-SSRS) [44], which will be used to assess suicide risk.Health service utilization outcomes: Health service utilization data will be extracted by the registration, reporting, and analytics, mental health and addiction team from the multiple health information systems utilized across NS Health and provided to the research team through reports. The differences in health service utilization data (mobile crisis visits, number of ED presentations, number of admissions in the last 12 months, length of stay, and the number of hospital readmissions) will be evaluated for participants in both groups. The differences between groups will be evaluated at 12 months.Patient experience and satisfaction outcomes: Patient satisfaction and patient experience with the e-mental health interventions (Text4Support and other e-mental health programs offered freely through NSH Authority) will be evaluated using both quantitative and qualitative data. Overall satisfaction will be assessed at each of the four time points (6 weeks and 3, 6, and 12 months) using a self-designed scale. Self-reported retention and withdrawal will both be assessed through the satisfaction survey, which addresses questions about the frequency of reading messages, the frequency of returning to messages stored in their phones, and actions taken by the participants after reading the text messages or freely available e-mental health resources (i.e., text “STOP”, clicking on links, searching for more information) up to 12 months after enrolment. Patient experience and satisfaction qualitative data will be collected through individual interviews and focus groups.Implementation Outcomes: Implementation outcomes are indicators of implementation efforts and are distinct from service or clinical outcomes [45]. For the intervention arm, we will include the reach of the interventions, acceptability, appropriateness, fidelity, and cost-effectiveness, evaluated at each of the four time points [28]. These implementation indicators will not be collected from the e-mental health or website visits in the control arm because they are not tied to the patient’s study ID and cannot be linked to the other measures.

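### With about 80% of primary survey data expected to be missing, most of the named sensitivity analyses cannot show whether the multiple-imputation result is robust; a tipping-point analysis should replace them

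*Protocol article*

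**What the plan says.** - **Expected response (2.3).** The premise is "Given that the maximum survey completion rate for the online surveys delivered via text message is approximately 20" per cent. From it, "we plan to enrol at least 1500 participants in the RCT", "in order to achieve 262 completed survey responses at each time point".
- **Primary scales (2.6, Table 1).** RAS and WHO-5 are the primary clinical outcomes. Both are marked as completed online by the patient.
- **Follow-up (2.4.4).** Survey links go out by SMS to both arms. Those who do not respond get an SMS prompt two days later, followed by telephone contact, with the stated aim of limiting loss to follow-up. Separately, "The same clinician-rated scales completed at enrolment will be completed over the phone by a trained research team member". Neither type of call is said to collect RAS or WHO-5.
- **Analysis (2.7).** MI is the main approach, starting with 100 datasets and then more, with the assumptions to be informed by a study of missingness patterns. The sensitivity set is described as "including a comparison with the last observation carried forward, mean/median imputation, best case, worst case, and complete case analyses". The investigators undertake to explain in the paper why approaches disagree.

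**The concern.** Over-enrolment fixes the number of completers, not who they are. If four in five participants give no primary outcome at a visit, the treatment estimate depends mainly on what is assumed about them. Non-response may well differ by arm: participants are not blinded (2.1), the survey arrives by text, and one arm receives daily texts for six months while the other receives a single text (2.5).

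The sensitivity analyses therefore have to show how far the assumption about non-responders can be moved before the conclusion changes. If the named methods give poor answers at 80% missing whatever the truth, disagreement between them reflects the methods rather than the data. The primary result could then be shown neither robust nor fragile.

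**Working it through.** **Inputs.** Completion c = 0.20 at most, so missing share m = 0.80 (2.3). Enrolment is 1500 (2.3), allocated 1:1 (2.1), so 750 per arm. The effect is 2 points, from "mean change score of 10 vs. 8" (2.3). Alpha is 0.05, two-sided (2.3).

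**1. The plan's own figures.** "an estimated sample size of 131 participants in each arm of the study would be needed", so 2 × 131 = 262 completers. Then 262/0.20 = 1310, below the 1500 planned. At 20% completion, 1500 × 0.20 = 300 complete and 1200 are missing; 262/1500 = 17.5% completion would meet the target. The enrolment step is consistent. The 131 itself is 2(1.960 + 1.282)² × SD²/2², which gives 131.3 with SD 5 but 27 (rounded up) with the stated variance of 5.0. That is a separate matter; below, the SD enters only where step 6 restates points as SDs.

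**2. Mean imputation within arm.** Filling 80% of values with the arm mean leaves a sample variance of about c·SD².
- SE reported: SD·√c·√(2/750). True SE: SD·√(2/(750c)). Ratio = c = 0.2.
- Type I error: 2[1 − Φ(1.96 × 0.2)] = 2[1 − Φ(0.392)] = 0.695.
- Simulation of change scores (750 per arm, 20% complete at random, 4000 runs, t-test): 69.3%.

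**3. Mean imputation from the pooled sample.** Responders differ by 2 and imputed values by 0, so the estimate is 0.2 × 2 + 0.8 × 0 = 0.4 (simulated 0.395).

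**4. Last observation carried forward.** A non-responder with no earlier follow-up response has baseline carried forward, hence zero change. If that holds for all 80%, the estimate is again 0.2 × 2 = 0.4 (simulated 0.395). This is the limiting case; earlier responses would soften it at later visits.

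**5. Best and worst case.** Let R be the range of the outcome and d the observed difference. Opposite extremes in the two arms give bounds of 0.2d ± 0.8R, a width of 1.6R.
- Since |d| cannot exceed R, 0.2|d| ≤ 0.2R < 0.8R: the bounds span zero whatever is observed.
- For a prevalence difference, the bounds are 0.2d ± 80 percentage points.
- For a mean, assuming R = 20 points (the document gives no range for the change scores): 0.4 ± 16, or −15.6 to +16.4.
- If instead the same extreme is imputed in both arms, the effect shrinks to 0.2 × 2 = 0.4.

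**6. What needs testing.** Shifting non-responders in one arm by δ moves that arm's mean by m·δ. A 2-point MI estimate is cancelled when m·δ = 2, so δ = 2/m:

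| Missing | Cancelling shift (points) |
|---|---|
| 80% | 2.5 |
| 50% | 4 |
| 20% | 10 |

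At 80% missing, 2.5 points is 0.5 SD if SD is 5, or 2.5/2.236 = 1.1 SD if the variance is 5.0.

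**7. More imputations.** Going beyond 100 datasets reduces Monte Carlo error only; it says nothing about δ.

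**The case against.** Several points against this have force.

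- **The list is open, and missingness patterns will be studied.** The wording does not claim to be exhaustive, and 2.7 never states missing at random. An unseen analysis plan may add more. This stands as to omissions. The point here is what the article does fix: of the methods named, one shares standard MI's ignorability assumption and the others break down. Patterns in the observed data cannot reveal how non-responders differ on unobserved scores.
- **Best and worst case do depart from missing at random.** True; the objection is that they are uninformative at this level.
- **The figures are particular cases.** Section 2.7 does not say whether means are taken within arm or pooled, so both are shown. The LOCF figure is a limiting case.

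A reader might also infer stronger things that the document does not support:

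- *That phone calls are not used against survey loss.* Section 2.4.4 plans exactly such calls. What can be said is that neither these nor the C-SSRS calls are stated to collect RAS or WHO-5, and 2.3 does not say whether the 20% allows for them.
- *That the main analysis has a 70% type I error.* That figure belongs to one sensitivity comparison under one reading.
- *That power fails if response falls below 20%.* Such a calculation needs SD 5, whereas the text states a variance of 5.0.
- *That this also settles retention.* Section 2.6 says "Self-reported retention and withdrawal will both be assessed through the satisfaction survey", which is open about being self-report. It is a separate matter, and a remedy would need platform logs that the document does not describe.

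**Conclusion.** The point holds in this form. About 80% missing on the primary scales is the plan's own planning figure. MI as the main method and complete case as a check are sound choices, but both rely on ignorable missingness. LOCF, mean/median imputation and best/worst case cannot serve as robustness checks here: a five-fold understated standard error, an effect shrunk from 2 to 0.4, or bounds that always include zero. Meanwhile a shift of 2.5 points among one arm's non-responders would cancel the hypothesised effect, and no named analysis examines it.

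This rests on 20% completion in both arms after any phone reminders, and on a 2-point effect. If calls raised completion to 50%, the cancelling shift would be 4 points and the need would be less acute; the document gives no recovery rate. Differential non-response is plausible from the design but not shown.

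**What to change.** 1. **Analysis.** Keep MI as the main method and complete-case ANCOVA as a sensitivity analysis. Replace LOCF, mean/median and best/worst case with arm-specific delta-adjusted MI. Vary δ in each arm separately and report the values at which the conclusion changes, for RAS and WHO-5.
2. **Imputation model.** Add the 12-month administrative utilisation data as auxiliary variables; 2.6 obtains these for both arms without a survey.
3. **Secondary suggestion, data collection.** Allow RAS (20 items) and WHO-5 (5 items) to be completed on the reminder or C-SSRS calls already planned, and record the mode. If only online non-responders answer by phone, mode is confounded with non-response and cannot simply be adjusted away, so show results with and without phone-collected data.

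Items 1 and 2 change analysis wording only and should be settled before outcome data are seen. Item 3 adds 25 items to some calls; staff time and likely recovery are not given in the document. It must be in place while follow-up is running, because outcomes never asked for cannot be recovered later.

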#### 2.4.2. Baseline Assessment

After providing consent, all subjects will be asked to complete an online baseline survey. The baseline survey includes sociodemographic information and self-completed validated scales designed to assess the patient’s mental health outcomes. During the baseline assessment, participants will be given the option of selecting the message bank from which they want to receive text messages based on their needs (i.e., depression, anxiety, bipolar disorder, etc.). In addition to that, one clinician-rated scale, which evaluates suicidal risk, will be completed by a trained research team member in person or over the phone. The average time for completing the baseline survey is 10 min.

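### The secondary prevalence outcomes are defined as change from baseline, but the only test named for them uses no baseline information; the cost is efficiency and alignment, not validity

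*Protocol article*

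**What the plan says.** Section 2.6 (Outcome Measures) gives the secondary clinical outcomes as "the differences between the intervention and control groups in prevalence changes for moderate-to-high depression", likewise for anxiety, and for "low resilience from the baseline to these time points". The time points are 6 weeks and 3, 6 and 12 months. The scales are PHQ-9, GAD-7 and BRS.

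Section 2.7 (Data Analysis) has one sentence on the binary versions of these scales: "We will also compare the prevalence scores for the clinical variables of interest using Chi-square" or Fisher's exact tests. It mentions no baseline term, change measure or model. The same section analyses the continuous scores of these scales at each time point by ANCOVA, with "the baseline scores on clinical variables as the covariate".

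The baseline is available. Section 2.4.2 says "After providing consent, all subjects will be asked to complete an online baseline survey", section 2.4.3 places enrolment after that survey is completed, and Table 1 lists all three scales at baseline and at every follow-up.

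**The concern.** The outcome is described as a change from baseline, yet the test named for it takes nothing from baseline. The continuous analysis of the same questionnaires does adjust, so the plan treats two versions of the same data differently without giving a reason.

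Two things are at stake. The reported result, a comparison of percentages, would not visibly correspond to the outcome in section 2.6. And baseline severity, where it predicts later severity, explains part of the variation in follow-up status. Leaving it out gives up power that needs no further data.

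The chi-square sentence does not itself say when the test is applied. That it compares the arms at each follow-up time is read from the time points in section 2.6 and from the neighbouring ANCOVA sentence.

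**Working it through.** **1. Numbers per arm.** Section 2.3 sizes the trial for the continuous primary outcomes only, with "a 2-sided significance level (α = 0.05), a power of 90"% and a difference of 2 (10 vs 8). The formula n = 2 × [SD × (1.960 + 1.282) / difference]² with SD = 5 gives 2 × (5 × 3.242 / 2)² ≈ 131.3. This reproduces the stated 131 per arm, provided the quoted spread of 5.0 is read as an SD. Read literally as a variance it gives 27 per arm, which is a separate matter. Enrolling 1500 with about 20% completion gives 1500 × 0.20 = 300 completers, or 150 per arm. So 131 to 150 completers per arm is the relevant range. The article gives no power for the prevalence outcomes.

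**2. Assumptions not in the documents.** Baseline prevalence 60%; follow-up prevalence 50% (control) vs 35% (intervention); correlation between baseline and follow-up score 0.3, 0.5 or 0.7; normally distributed scores cut at a threshold; no missing data. The move from 50% to 35% is a shift of z(0.65) − z(0.50) = 0.385 SD.

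**3. Chi-square by formula, 131 per arm.** The mean proportion is 0.425.
- Null SE = √(2 × 0.425 × 0.575 / 131) = 0.0611.
- Alternative SE = √((0.25 + 0.2275) / 131) = 0.0604.
- Power = Φ[(0.15 − 1.96 × 0.0611) / 0.0604] = Φ(0.50) ≈ 69%.

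**4. Simulation, 131 per arm, 3000 trials per row (power, %).**

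| Correlation | Chi-square | Raw change in prevalence | Logistic, baseline status | Logistic, baseline score | Gain, score vs chi-square |
|---|---|---|---|---|---|
| 0.3 | 70.8 | 51.6 | 71.6 | 72.8 | 2.0 |
| 0.5 | 72.6 | 57.2 | 75.0 | 77.9 | 5.3 |
| 0.7 | 71.8 | 66.8 | 80.5 | 85.8 | 14.0 |

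With no treatment effect, rejection rates were 4.5% to 6.0% over all methods: 5.4% to 5.5% for chi-square and 4.8% to 5.3% for logistic regression with the baseline score. The mean estimated effect was about −0.15 both for follow-up prevalence and for change in prevalence.

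**5. Second simulation, 150 per arm, 1500 trials per cell, cut-off near the control median.**
- Shift 0.4 SD: chi-square 79.1, 78.3 and 79.1% vs logistic 84.1, 86.7 and 90.6% at correlations 0.5, 0.6 and 0.7. Gains are 5.0, 8.4 and 11.5 points.
- Shift 0.3 SD: 56.1, 55.1 and 56.7% vs 61.7, 66.8 and 72.0%. Gains are 5.6, 11.7 and 15.3 points.

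**6. Range.** A further run over 131 to 150 per arm and shifts of 0.3 to 0.4 SD gave gains of about 0 to 2 points at correlation 0.3, 3 to 6 at 0.5 and 11 to 17 at 0.7, with type I error near 5% for both tests.

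**7. Why a raw change test is no remedy.** In the control arm of step 4, the variance of follow-up status is 0.25. The variance of change is 0.24 + 0.25 − 2φ√(0.24 × 0.25), where φ is the correlation of the two binary statuses. The simulated φ of 0.19, 0.31 and 0.46 give about 0.40, 0.34 and 0.26, all above 0.25. Subtracting baseline status adds noise; adjusting for the baseline score removes it.

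**The case against.** The strongest reply is that the chi-square does serve the stated outcome. Arms formed by 1:1 randomisation have the same expected baseline prevalence, so the between-arm difference in follow-up prevalence equals in expectation the difference in prevalence change. The simulations bear this out. A reader might infer that the test addresses the wrong hypothesis; the documents do not support that. Logistic regression on follow-up status is no more literally a test of change than the chi-square is. This part of the objection stands, and it limits the point to efficiency and alignment.

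Second, section 2.7 already plans a baseline-adjusted ANCOVA of the same scales, and the prevalence comparison accompanies it. In the step 4 scenario that ANCOVA has 90.3, 94.8 and 99.1% power at the three correlations. This also stands and keeps the consequence modest. It does not explain why the binary versions, which are the secondary outcomes named in section 2.6, should go without the covariate.

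Third, a reader might infer that imbalance among the roughly 20% who respond is left unaddressed. The plan makes multiple imputation its main approach, adds an analysis of missingness patterns and several sensitivity analyses, and uses reminders and phone calls. A reader might also infer that Fisher's test cannot be combined with the 100 imputed datasets. How results are pooled is commonly left to the analysis plan, which is not shown, and a difference in proportions with its standard error pools by the usual rules. Neither inference is a finding here.

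**Conclusion.** The point holds in limited form. Section 2.6 defines a change from baseline, and section 2.7 names only tests that ignore baseline, while adjusting for it in the continuous analysis of the same scales. The chi-square remains valid for the same null under randomisation; the defect is lost efficiency and a poor fit between definition and analysis.

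The size depends on inputs that the documents do not give. Under the assumptions above, the gain runs from about 0 to 2 points of power at a baseline correlation of 0.3 to about 11 to 17 points at 0.7. Quoting only the upper correlations would overstate it. The simulations cover completers without missing data, so they do not measure the gain after multiple imputation. These are secondary outcomes, and the change is worth making because it is specific and costs almost nothing.

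**What to change.** In section 2.7, replace the chi-square/Fisher sentence for these outcomes. At each follow-up time, analyse each of the three binary outcomes by logistic regression on treatment, with the continuous baseline score of the same scale as covariate. Use the score rather than baseline status: in step 4, status recovered only 0.8, 2.4 and 8.7 points.

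Report a standardised risk difference with 95% CI, pooled over the imputations, since the adjusted odds ratio is not itself a difference in prevalence. State that under randomisation this estimates the between-arm difference in prevalence change defined in section 2.6. Keep raw percentages by arm, including baseline, as description.

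Do not substitute an unadjusted test of raw prevalence change; it was weaker than the chi-square at every correlation tried.

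The cost is a change of wording. No new data, visits or participants are needed.

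### The exploratory two-way ANOVA for demographic and clinical factors omits the baseline score, so its factor term can reflect differences at entry and any treatment-by-factor test is less precise than it could be

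*Protocol article*

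**What the plan says.** Section 2.7 (Data Analysis) specifies two models for the rating scales.

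- **Arm comparison.** An ANCOVA of the two arms, whose remaining terms are given thus: "the baseline scores on clinical variables as the covariate, and the scores at each time point on standardized rating scales as the dependent variable".
- **Demographic and clinical factors.** A plain ANOVA is announced here: "To explore the impact of select demographic and clinical variables on the clinical variables of interest, we will perform a two-way between-groups". No covariate is named. The sentence does not name the two factors, say that treatment is one of them, mention an interaction, or say whether the dependent variable is a follow-up score or a change.

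Section 2.6 (Outcome Measures) frames effectiveness relative to baseline: "The intervention effectiveness will be determined by evaluating the differences between the intervention and control group from baseline and the subsequent time points". It also defines the primary outcome as a change: "The primary clinical outcome will be the differences in mean change in patient recovery and quality of life". Section 2.2 enrols both first-time outpatients and patients about to leave inpatient units. Table 1 lists a baseline and four follow-up assessments for RAS, WHO-5, PHQ-9, GAD-7, BRS, BSCS and C-SSRS. The ACE questionnaire is collected at baseline only.

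**The concern.** Baseline adjustment is planned where randomisation already balances the groups on average, and is absent where nothing balances them. Age group, sex, diagnosis and route of entry are not randomised, and groups defined by them may well start at different levels on these scales. An unadjusted factor term carries that starting gap into the follow-up comparison, yet the plan describes its target as *impact*. A published statement that a diagnosis or entry route affected outcome could then rest on where the groups began.

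If the second factor is treatment, the natural exploratory question is whether the factor modifies the effect of Text4Support. That test stays valid without the baseline score, but it carries between-person variance that a measurement already in hand would remove.

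**Working it through.** **The plan's own figure.** Section 2.3 gives 131 per arm for a 2-point difference ("e.g., mean change score of 10 vs. 8"), two-sided α = 0.05 and 90% power. The formula is n = 2(1.960 + 1.282)²σ²/δ².
- With σ = 5 and δ = 2: 2 × 10.507 × 25/4 = 131.3, which matches.
- With "a population variance of 5.0 for the mean change score" read literally: 2 × 10.507 × 5/4 = 26.3, so 27 per arm. The figure of 131 therefore needs 5.0 to be an SD. That is a separate matter; it is used here only to fix N = 262.

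No figure is stated for the two-way ANOVA. At 20% completion, 1500 enrolled gives 300 completers per time point. N = 1500 would apply only if the imputed data were treated as complete.

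**Assumptions, not in the documents.** Two-level factor split evenly; 1:1 treatment; within-group SD of 1; baseline-to-follow-up correlation r from 0.3 to 0.7; baseline gap g between factor levels of 0.2 or 0.5 SD; no factor effect on follow-up given baseline.

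**Factor term, follow-up scores.** The expected estimate is r × g, with SE = 2/√N = 2/√262 = 0.124 SD. For g = 0.5 and r = 0.7: 0.35/0.1236 = 2.83, so the term rejects in about 81% of trials. For g = 0.2 and r = 0.3: 0.06/0.1236 = 0.49, so about 8%. Simulation (1500 runs per setting) gave:

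| N | g (SD) | r = 0.3 | r = 0.5 | r = 0.7 |
|---|---|---|---|---|
| 262 | 0.2 | 8% | 13% | 19% |
| 262 | 0.5 | 21% | 51% | 80% |
| 1500 | 0.2 | 20% | 51% | 76% |
| 1500 | 0.5 | 83% | >99% | 100% |

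With the baseline covariate the rate was 4-6% throughout.

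**Factor term, change scores.** The expected estimate is −(1 − r) × g, opposite in sign to the baseline gap, with SE = 2√(2(1 − r))/√N. For g = 0.5 and r = 0.3 at N = 262: 0.35/(0.1236 × 1.183) = 2.39, so about 67%. Simulated rates at g = 0.5 and N = 262 were 64%, 50% and 35% for r = 0.3, 0.5 and 0.7.

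**Treatment-by-factor term, if treatment is one factor.** Without the covariate, SE = 4/√N = 4/√262 = 0.247 SD. With it, SE = 0.247 × √(1 − r²). For a 0.5 SD interaction:

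| Model, N = 262 | SE | z | Power |
|---|---|---|---|
| No covariate | 0.247 | 2.02 | about 52% |
| Covariate, r = 0.3 | 0.236 | 2.12 | 56% |
| Covariate, r = 0.5 | 0.214 | 2.34 | 65% |
| Covariate, r = 0.7 | 0.176 | 2.83 | 81% |

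For a 0.4 SD interaction at N = 262, power is 37% without the covariate and 40%, 46% and 62% with it. At N = 1500 it is 97% against 98-100%. Change scores do not recover the precision: for 0.4 SD at N = 262 they gave 27%, 37% and 56%, against 41%, 45% and 62% for ANCOVA in the same simulations.

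**The case against.** **The analysis is exploratory and condensed.** It has no stated hypothesis and no role in the sample size, and a journal article may leave model detail to a fuller plan. This limits the weight of the point. It does not remove it, because the article names a specific model without a covariate just after naming one with a covariate.

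**Rejecting is not an error for the null that ANOVA tests.** If groups differ at follow-up by r × g, their score levels really are unequal. The rates above count as false only for the question of course given baseline. Adjusting for baseline also changes the question for demographic factors that precede it. This stands as a caution. The difficulty is that the plan calls the result an impact, which neither model's factor term can establish.

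**Stronger inferences that the documents do not support.**
- A reader might infer that the factor term mostly tests who was sicker at entry. That depends on r and g, which are not given; with a small gap and low correlation the distortion is slight. Under a change-score reading the mechanism is regression to the mean instead.
- A reader might infer that a planned interaction test will miss real differences in response. No such test is stated, and the precision loss runs from negligible to marked depending on r and N.
- A reader might infer that this ANOVA alone addresses the evidence gap on diagnoses and levels of care. The Introduction states that aim as efficacy on transdiagnostic outcomes against usual care, which is addressed mainly by the baseline-adjusted arm comparison.

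**Conclusion.** The point holds as a limited one about an exploratory analysis. The stated two-way ANOVA leaves out the baseline score, and under either reading of the dependent variable its non-randomised factor term does not isolate the factor's relation to course. At N = 262 the follow-up-score version rejects in about 8% to 80% of trials over gaps of 0.2-0.5 SD and r of 0.3-0.7, and a larger N worsens this. If treatment is one of the factors, its interaction test is unbiased. Omitting the covariate costs about 12 to 28 percentage points of power at N = 262 for a 0.5 SD interaction with r = 0.5-0.7, about 4 points at r = 0.3, and almost nothing at N = 1500. All of these sizes rest on assumed correlations, gaps and an even two-level split. The treatment comparison by ANCOVA is not affected.

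**What to change.** In section 2.7, replace the two-way between-groups ANOVA with a two-way ANCOVA: score at each time point on treatment, factor and treatment × factor, with the baseline score of the same scale as covariate. Restrict it to scales measured at both baseline and follow-up, which excludes the ACE questionnaire as an outcome. State the dependent variable. Use the interaction term as the exploratory test of whether the factor modifies the effect of Text4Support. Report the factor's own term as a baseline-adjusted association, not as an impact.

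The cost is a short change of wording. The baseline scores are already collected and already used in the main ANCOVA, so no extra data or participants are needed.
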